### Secondary outcomes

Secondary outcome measures include: (i) the SF-36 questionnaire [36,37], (ii) procedure complications, (iii) pain, measured by the VAS [33], (iv) Constant questionnaire functional score [38]; (v) radiographic characteristics in terms of (a) consolidation of the fracture and (b) displacement and angulation of the fracture fragments.

The SF-36 is a questionnaire containing 36 items. This survey assesses eight health concepts: physical functioning, bodily pain, limitations due to health problems, limitations due to personal or emotional problems, emotional well-being, social functioning, energy/fatigue and general health perceptions. The VAS consists of a 10-cm line anchored by two extremes: ‘no pain’ and ‘pain as bad it could be’. Patients are asked to make a mark on the line, which represents the intensity level of their perceived pain, and the scale is scored by measuring the distance from ‘no pain’ to the patient’s mark.

Consolidation will be considered as a dichotomous variable: fracture healing or no healing. Displacement and angulation of bone fragments will be measured on radiographs.

### Data analysis

Patients, who for any reason demonstrate that their treatment may require additional interventions, will be followed up, and their results will be included in the group into which these patients had initially been randomised, according to the intention-to-treat principle. The Pearson chi-squared test will be used to analyse the results from the two groups in relation to the categorical variables, and Student’s *t*-test will be used to compare the groups in relation to the numerical variables. Student’s *t*-test (parametric) will be used to compare the clinical evolution of each group 2, 4, 8, 24 and 48 weeks after the intervention. For the primary outcome, a significance level of 5% (alpha = 0.05) will be used for all statistical tests, such that tests presenting a *P*-value less than 0.05 will be considered statistically significant. For the secondary outcomes we will consider an alpha value of 0.02.

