## Background

Humeral shaft fractures account for 1 to 3% of all fractures in adults [1,2] and for 20% of all humeral fractures [3]. These fractures have an annual incidence from 13 to 14.5 per 100,000 people [4,5]. Non-operative treatment is still the standard treatment for isolated humeral shaft fractures [6,7], although this method can present unsatisfactory results, such as, nonunion and shoulder impairment [8,9]. Fourteen percent of patients treated with this method have restricted range of motion and 12.6% have consolidation, with more than 10° of displacement [10].

Surgical treatment is recommended for patients with neurovascular injuries, medullar or brachial plexus injuries, and open fractures, for patients with multiple injuries, and for floating elbow and unsatisfactory reductions [11-13]. Humeral shaft fractures can also be treated surgically for the following indications: *Arbeitsgemeinschaft für Osteosynthesefragen* (AO)-Orthopaedic Trauma Association (OTA) type A fractures, proximal third oblique fractures and distal third shaft fractures [14-16]. Surgical options for treatment of humeral shaft fractures include open reduction and internal fixation with a compression plate, intramedullary nail osteosysthesis and minimally invasive bridge plate fixation. Open reduction and rigid internal fixation with absolute stability using dynamic compression plates [17-19] is today’s standard and is the more common surgical option for treatment of these fractures.

Modern concepts of internal fixation of shaft fractures of the long bones advocate relative stabilisation techniques with no harm to the fracture zone. These have largely been used for fractures of the leg and thigh for which they have become the gold standard treatment. In humeral shaft fractures, these concepts are also being applied with the use of the intramedullary nail [20-22]. In a systematic review, when compared to compression plate osteosynthesis, the use of the intramedullary nail presented a higher risk of shoulder impingement, shoulder pain, and restriction of movements [23]. Recently described by Livani and Belangero [24], minimally invasive bridge plate osteosynthesis with anterior access has been shown to be a secure technique with good results for the majority of humeral shaft fractures [25-27].

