### Sample size

The sample size was calculated for a significance level of 0.05, statistical power of 90% and SD of 15% in Disability of the Arm, Shoulder and Hand (DASH) scores and an absolute difference between the groups of 10 points in the DASH scores. It was calculated that 50 patients were needed in each group [30,31]. Allowing for a 10% loss to follow up at 24 weeks, we aim to recruit a total of 110 patients.

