### Randomisation and allocation

The randomisation sequence will be generated by computer software (http://www.randomizer.org), creating a list from 1 to 110, each number being related to one of the two proposed methods of treatment. We will perform simple (unrestricted) randomisation, making the intervention assignment unpredictable, including the last 10 participants. According to this list, inside each of the 110 opaque sealed envelopes numbered from 1 to 110, will be a piece of paper containing the words ‘functional brace’ or ‘bridge plate.

Participant allocation will be performed after explaining the protocol and describing both of the procedures to be randomised, and after participants have agreed to take part and signed the informed consent form (Additional file 1 and Additional file 2). They will also be clinically evaluated to determine whether they are suitable candidates for surgery. After this, an independent person will open the envelope before proceeding to the intervention (Figure 1).

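### Student's t-test is named for all numerical outcomes under simple randomisation; naming Welch's version would guard against unequal spread at almost no cost

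*Protocol article*

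**What the plan says.** In the protocol article, the Data analysis section names one test for every numerical outcome: Student's t "test will be used to compare the groups in relation to the numerical variables". It names Student's t again for the follow-up visits, where it "will be used to compare the clinical evolution of each group 2, 4, 8, 24 and 48 weeks after the intervention". It mentions no variance check and no alternative test. The significance level is 5% for the primary outcome and 2% for the secondary outcomes.

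The Randomisation and allocation section states: "We will perform simple (unrestricted) randomisation, making the intervention assignment unpredictable, including the last 10 participants". There is no blocking, so nothing forces the arms to be equal.

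The Sample size section uses a "significance level of 0.05, statistical power of 90% and SD of 15", the same SD for both arms, with "an absolute difference between the groups of 10 points in the DASH scores". It concludes: "It was calculated that 50 patients were needed in each group". No section gives an SD by arm.

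**The concern.** Student's t-test estimates one variance from both arms together. This does no harm if the arms have the same variance, and very little if they have the same size. When both differ, the pooled standard error is too small if the more variable arm is the smaller one, and too large if it is the bigger one. The plan gives up assured equal sizes by choosing simple randomisation, and so relies on equal spread.

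At stake is whether the stated 5% and 2% levels, and any confidence interval built on the pooled standard error, hold for the split that actually occurs. The direction of any error cannot be known before the arms are filled.

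**Working it through.** **1. The plan's own figure.** Inputs from the Sample size section: difference 10, SD 15, alpha 0.05 (taken as two-sided), power 90%. The normal formula gives n = 2 × (1.960 + 1.282)² × 15² / 10² = 47.3, so 48 per arm. The t-based solution is 48.3, so 49. The stated 50 is consistent with both and has 91.0% power. With the planned 10% loss, 110 × 0.9 = 99 patients remain evaluable. The sample size is not in question.

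**2. How unequal the arms may be.** Under simple randomisation the size of one arm is Binomial(N, 0.5).
- All 110 patients: the chance of exactly 55/55 is 7.6%.
- 99 evaluable: the chance of 46/53 or worse is 2 × P(n1 ≤ 46) = 55%.
- 99 evaluable: the chance of 43/56 or worse is 2 × P(n1 ≤ 43) = 22.8%.

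**3. Effect on the standard error.** Write s1, s2 for the SDs and n1, n2 for the arm sizes.
- True variance of the difference: V = s1²/n1 + s2²/n2.
- What the pooled test targets: P = [((n1 − 1)s1² + (n2 − 1)s2²) / (n1 + n2 − 2)] × (1/n1 + 1/n2).
- Large-sample size of the nominal 5% test: 2Φ(−1.960 × √(P/V)).

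The SD ratios are assumptions, because the document gives only the common value. Example with ratio 1.5 and the more variable arm being the smaller one (43 against 56):
- V = 2.25/43 + 1/56 = 0.0702.
- P = (42 × 2.25 + 55 × 1)/97 × (1/43 + 1/56) = 1.541 × 0.0411 = 0.0634.
- √(P/V) = 0.950, so the size is 2Φ(−1.862) = 6.3%.

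**4. Results at nominal 5%.** In each cell the first figure is for the larger SD in the smaller arm, the second for the larger SD in the bigger arm. Simulations use normal data, 60,000 runs per case.

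| Split | SD ratio | Student, formula | Student, simulated | Welch, simulated |
|---|---|---|---|---|
| any | 1 | 5.0% | – | – |
| 46/53 | 1.5 | 5.7% / 4.4% | – | – |
| 46/53 | 2 | 6.0% / 4.1% | – | – |
| 43/56 | 1.5 | 6.3% / 3.9% | 6.2% / 3.9% | 4.9% / 4.9% |
| 43/56 | 2 | 7.0% / 3.4% | 7.1% / 3.5% | 4.9% / 5.0% |

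At the 2% level used for secondary outcomes, replacing 1.960 by 2.326 in the formula gives, at 43/56, 2.7% / 1.4% for ratio 1.5 and 3.2% / 1.2% for ratio 2.

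**5. Averaged over splits.** Weighting the formula by the binomial probabilities at N = 100 gives a size of 5.05% for SDs 12 and 18 and 5.12% for SDs 10 and 20. The deviations in the two directions almost cancel. The problem therefore belongs to the realised split and not to the design as a whole.

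**6. Cost of Welch with equal SDs.** For SD 15 and difference 10, simulated power is 91.1% for both tests at 50/50, and 89.8% (Student) against 89.7% (Welch) at 60/40.

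**The case against.** The strongest reply is that unequal spread is nowhere shown. The Sample size section assumes one SD, no section gives an SD by arm, and with equal SDs Student's test is exact at any split. This stands, and it is why the point is conditional.

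A reader might infer from the Background that the brace arm is likely to be more variable, because "Fourteen percent of patients treated with this method have restricted range of motion" and 12.6% heal with more than 10° of displacement. The document does not support that step. These are proportions and not DASH values, they have no plate-arm counterpart, and the Safety section lists expected complications for both groups, including hardware failure, infection, malunion and nonunion. A reader might also suppose that a plate gives much tighter angulation, with an SD ratio as high as 3. That is conjecture too, and no figure for it is used here.

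A second reply is that if treatment affected no one, the two distributions would be identical and Student's test valid; inflated size needs equal means with unequal variances. This narrows the case for the test. It does not remove the point for the confidence interval, whose coverage depends on the standard error whatever the true difference.

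A third reply is that the effect is small. Inflation at 43/56 or worse also requires the more variable arm to be the smaller one, which halves 22.8% to about 11%. This stands.

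A fourth reply is that a condensed article may leave variance handling to the analysis plan, and that the words equal-variance or pooled never appear. This is fair in part. However, the article does name a test, by ordinary usage the pooled one, so the point concerns a stated choice and not an omission.

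**Conclusion.** The point holds as a low-severity robustness improvement. Two stated choices, Student's t-test and simple randomisation, together leave the standard error unprotected if the arms differ in spread. Assuming an SD ratio of 1.5 to 2 and a 43/56 split, the nominal 5% test has a true size of about 6 to 7% or 3.5 to 4%, depending on which arm is smaller. At the more typical 46/53 it stays between about 4.1% and 6.0%.

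The conclusion rests on assumed SD ratios, normal data, 99 evaluable patients and the usual meaning of Student's t-test. It does not show that the arms will differ in spread, that the trial's overall type I error is materially inflated, or that any stated figure is wrong. A reader might infer these, but the document supports none of them.

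**What to change.** In the Data analysis section (or in the analysis plan, before unblinded data are seen), replace Student's t-test by Welch's unequal-variance t-test with the matching confidence interval. Apply this to the between-group comparison of the 6-month DASH and of the numerical secondary outcomes.

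The cost is a change of a few words. With equal SDs, power changes by less than 0.1 percentage point, and the planned 50 per group and 110 in total stay as they are. With unequal SDs the two tests can differ in power: at 60/40 with SD 12 in the arm of 60 and 18 in the arm of 40, simulated power is 89.3% for Student and 86.0% for Welch. Student's advantage there comes with a true size of about 7%. With the SDs the other way round, Welch is the more powerful (91.1% against 88.2%).

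### Visit-by-visit t-tests leave the early DASH scores of lost patients unused; one repeated-measures model would be a cheap safeguard for the 6-month primary result

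*Protocol article*

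**What the plan says.** All statements are in the protocol article.

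- **Data analysis.** Numerical variables are compared between the groups with Student's t-test. A further sentence says the t-test "will be used to compare the clinical evolution of each group 2, 4, 8, 24 and 48 weeks after the intervention". No longitudinal model is named.
- **Primary outcome.** DASH at 6 months after the procedure.
- **Outcome assessment.** DASH is applied at 2 and 4 weeks and at 2, 6 and 12 months, so three DASH scores are scheduled before the primary visit. I take the 8, 24 and 48 weeks of the Data analysis section as the 2-, 6- and 12-month visits.
- **Sample size.** "Allowing for a 10% loss to follow up at 24 weeks, we aim to recruit a total of 110 patients".
- **Data analysis, on additional interventions.** Patients who may need further treatment are followed and analysed in their randomised group, "according to the intention-to-treat principle".

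**The concern.** A t-test at 6 months, applied to observed scores, uses only patients who have a 6-month score. For a patient lost between 8 and 24 weeks, up to three earlier DASH scores are in the database but do not enter the primary comparison.

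This matters if the patients lost from one arm were recovering unusually well or badly and the same is not true in the other arm. The remaining patients are then a selected group in one arm, and the 6-month difference is shifted. The arms are very different treatments, and patients know which they had: the blinding described under Outcome assessment covers assessors. Loss that differs by arm is therefore conceivable, although the article does not predict it.

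**Working it through.** **1. The plan's own figures.** Inputs from the sample size section: "The sample size was calculated for a significance level of 0.05" (taken as two-sided), "statistical power of 90% and SD of 15% in Disability of the Arm, Shoulder and Hand (DASH) scores" (read as 15 points) and "an absolute difference between the groups of 10 points in the DASH scores".

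- n per arm = 2 × (1.960 + 1.282)² × 15² / 10² = 2 × 10.51 × 2.25 = 47.3, so 48. The t-based calculation gives 48.3, so 49. The article states "It was calculated that 50 patients were needed in each group", which agrees.
- Loss: 100 × 1.10 = 110, as stated; 100 / 0.9 = 111.1, or 112 when rounded up to equal arms. The gap is trivial.
- With 50 completers per arm, power is about 91%, and the standard error of the difference is 15 × √(2/50) = 3.0 points.

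The sample size suits a single two-group comparison at 6 months and is not in question.

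**2. Bias of the observed-case t-test.** Assumptions not in the document:

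- early and 6-month DASH are jointly normal with SD 15 and correlation ρ of 0.3 to 0.7;
- in one arm, the log-odds of loss rise by 1 or 2 per SD of the early score, with the intercept set to give 10% loss;
- in the other arm, loss is unrelated to the score.

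Let z be the standardised early score. The mean 6-month score of those who remain shifts by ρ × 15 × E(z | remaining), where E(z | remaining) = −(0.10/0.90) × E(z | lost).

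| Logit slope | E(z, lost) | Size of E(z, remaining) | ρ = 0.3 | ρ = 0.5 | ρ = 0.7 |
|---|---|---|---|---|---|
| 1 per SD | 0.82 | 0.091 | 0.41 | 0.68 | 0.95 |
| 2 per SD | 1.28 | 0.143 | 0.64 | 1.07 | 1.50 |

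The last three columns are bias in DASH points. The range is 0.4 to 1.5 points, or 4% to 15% of the 10-point target and 0.14 to 0.5 of the standard error. Its direction depends on which arm loses which patients.

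**3. Using the early score.** I simulated two arms of 55 with a true difference of 10 and the loss pattern of step 2, with 10% random loss in the other arm. The t-test estimate averaged 9.6 to 8.4. The likelihood estimate that keeps the early score of lost patients averaged 9.9 to 10.1. This is a two-visit version of the repeated-measures model, not the full five-visit fit.

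**4. Other loss patterns** (true difference 10, slope 2, ρ = 0.3 / 0.5 / 0.7).

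| 10% loss | t-test | Likelihood estimate |
|---|---|---|
| Random | 10.0 / 10.0 / 10.0 | 10.0 / 10.0 / 10.0 |
| Linked to early score, same way in both arms | 10.1 / 10.1 / 10.0 | 10.1 / 10.1 / 10.0 |
| Linked to early score, opposite directions | 8.7 / 7.9 / 7.0 | 10.0 / 10.1 / 10.0 |
| Linked to the unseen 6-month score, opposite directions | 5.6 / 5.6 / 5.6 | 5.9 / 6.6 / 7.6 |

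The third row is an extreme case; there the power of the t-test falls to 82%, 75% and 65%. The last row shows the limit of the remedy.

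**5. Precision.** Under random 10% loss at ρ = 0.7, the SD of the estimate is 2.97 for the t-test and 2.92 for the likelihood estimate, a gain of under 2%.

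**The case against.** The strongest objection is that a t-test names a comparison and not a rule for missing scores. Multiple imputation from the earlier DASH scores, followed by t-tests, would fit the article's wording and use the same information. Such a rule commonly sits in an analysis plan, which is not shown. This stands as far as it goes: the article cannot be faulted for lacking a missing-data rule, and the bias above applies to the t-test used as stated on observed scores. It does not remove the case for a better primary method than the one named.

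It is also fair that every correlation and loss mechanism used here is assumed, and that the article does not say loss will differ by arm.

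A reader might infer more than the text supports:

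- **That the t-test is invalid because it ignores within-patient correlation.** The primary analysis is one between-arm comparison at one visit, with one score per patient. It is valid.
- **That any link between loss and recovery biases the result.** The second row of the table in step 4 shows none when the link to the early score is the same in both arms.
- **That the intention-to-treat statement contradicts the t-test.** That sentence concerns patients needing additional interventions and promises nothing about missing scores.
- **That unpaired tests within each arm over time are planned.** The sentence on clinical evolution is ambiguous. It can be read as between-arm comparisons at each visit, and it never says unpaired. No standard error penalty can be charged to the plan on that basis.

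**Conclusion.** The point holds as a cheap improvement. The article fixes a valid but less protective analysis for its primary outcome, although three earlier DASH scores are scheduled and 10% loss is expected.

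The exposure is about 0.4 to 1.5 DASH points if loss is linked to the early score in one arm only, given SD 15, 10% loss, correlation 0.3 to 0.7 and a logit slope of 1 to 2 per SD. It is nil if loss is random or linked in the same way in both arms. It reaches about 1.3 to 3.0 points only under opposite links in the two arms at slope 2.

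A reader might infer that a repeated-measures model would remove dropout bias altogether. It would not. It corrects bias under missing at random with a suitable model. When loss follows the unseen 6-month score, the bias is only reduced.

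**What to change.** 1. Make the primary analysis a mixed model for repeated measures on DASH, with arm, visit and arm-by-visit as fixed effects and an unstructured within-patient covariance. Include all randomised patients with at least one post-treatment DASH, in the arm to which they were randomised.
2. Report the arm contrast at 6 months with its 95% confidence interval as the primary result.
3. Keep the 6-month t-test as a sensitivity analysis.
4. Reword the sentence on clinical evolution so that it plainly means between-arm contrasts at each visit, taken from the same model.
5. State that the model relies on missing at random, and that patients with no DASH at all contribute nothing to it.

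**Cost:** a paragraph of analysis wording and slightly more programming. The sample size, visits and data collection do not change. The downside is reliance on the missing-at-random assumption, which the t-test kept alongside helps to put in view but does not test.

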### Safety

Rates of complications are part of secondary outcome analysis and will be closely monitored. Expected complications in both intervention groups include skin abrasion, skin pressure ulcers, forearm and hand swelling, sensomotor deficit, wound healing problems, hardware displacement and failure, superficial and deep infection, malunion, nonunion, and shoulder and elbow impairment. Complications will be categorized as minor or major according to their severity. Causes of complications will be studied and they will be treated as soon as detected. Complications that may lead to surgical intervention, surgical revision, or clinically important morbidity are classified as severe adverse events. This protocol does not include a data safety monitoring committee.

## Discussion

According to current evidence from a systematic review [28], this study is one of the first randomised controlled trials designed to compare surgical to nonsurgical management of humeral shaft fractures, to evaluate outcomes of quality of life, safety and effectiveness.

Despite the risk of a surgical intervention, the minimally invasive plate osteosynthesis technique seems to be reproducible and applicable in almost all types of humeral shaft fractures. It had the advantage of minimal soft tissue dissection and lower rates of iatrogenic nerve injury when compared to the conventional plate technique. Intramedullary nail osteosynthesis has resulted in higher rates of reoperations and shoulder impairment compared to the compression plate technique [23,25,27]. Functional bracing is a traditional method of treatment but can have some complications, such as, nonunion in proximal-third fractures, residual angulation of more than 10˚ and skin abrasion [16,39].

Fractures too proximal or too distal in the humeral shaft cannot be surgically treated with this minimally invasive technique, which is a limitation of this trial. Another limitation is the fact that this study will take place in only one centre. This not only impacts recruitment, but also may limit the generalisability of the results to other settings. However, the use of broad inclusion criteria is the strength of the trial.

This study aims to provide conclusive, good quality evidence for orthopaedic practice and will contribute to the evidence base of methods used to treat humeral shaft fractures.

